#### Depression, quality of life, and sleep

Depression will be assessed at baseline and the primary follow-up (Day 11) using the Major Depression Inventory (MDI) (53, 54), as depression is a key confounder due to its correlation with fatigue (83). Complementing the MDI, the Beck Depression Inventory-II (BDI-II) (84) will also be administered at both timepoints for cross-study comparability, and BDI-II data will only be reported descriptively.

The Multiple Sclerosis Impact Scale (MSIS-29) (85), and the Epworth Sleepiness Scale (ESS) (86) will be acquired at four timepoints [baseline; 1 day post-intervention (Day 6); primary follow-up (Day 11); and 4 weeks post-intervention (Day 33)], to assess the quality-of-life impact of MS (87), and undiagnosed sleep disorders (88), which might impact fatigue. Both scales will be analyzed as change-from baseline comparison between groups at the main clinical follow-up. Daily sleep quality ratings, integrated into the fatigue diary, will be analyzed analogously to diary-based fatigue scores.

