### Sample size calculation

Based on a clinical meaningful effect size of 10 points on the FSMC scale between baseline (D0) and the primary follow-up (Day 11) measurements, and assuming a standard deviation of 12.5 (20, 21, 108), the estimated sample size is 25 per arm and 50 participants in total. This will yield 80 % power of reaching evidence of a treatment effect, with a *p*-value under 0.05. Accounting for a drop-out of 15%, our final sample size is 29 per arm, 58 in total.

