#### Statistical methods and analysis

All variables will be visually inspected for normal distribution through histograms and quantile-quantile plots prior to analysis and appropriately transformed if necessary. If data diverge from the normal distribution after transformation non-parametric testing will be performed. All tests will be 2-sided and statistical significance will be set at a *p*-value < 0.05. Data will be analyzed with R (116), Matlab (The MathWorks Inc., Natick, MA, United States) or similar software.

All data will be analyzed as a modified intention-to-treat, where all participants who have undergone at least one rTMS session (active or sham) and have follow-up data for outcomes will be analyzed according to the group they were randomized to. No per-protocol analyses are planned. The primary outcome will be analyzed as difference in change between baseline and clinical follow-up, between active and sham group. The statistical significance will be assessed with a mixed-effects linear model with the baseline as the reference. The primary analysis model will not adjust for depression, sleep, or physical activity measures, as the study is powered to detect overall treatment effects rather than covariate-adjusted effects. These variables will be examined in exploratory analyses as potential modifiers of treatment response, to assess whether treatment effects differ according to baseline levels or changes in these factors. Secondary outcomes with two timepoints (baseline and follow-up), will be compared as the difference in change between groups. Secondary outcomes with more timepoints will be analyzed with mixed-effects linear models with the baseline as reference. Neither the pre-registered primary or main secondary outcomes will be corrected for multiple comparisons, except where appropriate due to multiple measurements per participant. Exploratory analyses will be appropriately corrected for multiple comparisons prior to reporting.

There are no plans for predetermined subgroup analyses.

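### Changes in depression, sleep and activity after randomisation are listed as effect modifiers; only the baseline levels can serve as such (exploratory analyses only, minor)

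*Protocol article*

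**What the plan says.** Statistical methods and analysis separates the primary model from these variables: "The primary analysis model will not adjust for depression, sleep, or physical activity measures". It then assigns depression, sleep and physical activity to exploratory analyses "as potential modifiers of treatment response, to assess whether treatment effects differ according to baseline levels or changes in these factors". On multiplicity it says "Exploratory analyses will be appropriately corrected for multiple comparisons prior to reporting".

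The timing of the measurements is given elsewhere in the article:

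- **Allocation.** Baseline behavioural and MRI assessments are finished before group assignment, and the envelope is opened on Day 1 (Allocation concealment and implementation).
- **Depression.** The MDI is taken at baseline and again on Day 11, the visit of the primary FSMC (Depression, quality of life, and sleep; Trial overview).
- **Sleepiness.** The ESS is taken at baseline and on Days 6, 11 and 33, and its change is compared between groups (Depression, quality of life, and sleep).
- **Activity.** The accelerometer is worn from baseline to follow-up, through the treatment week, and between-group differences are assessed (Accelerometer-based outcomes).

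The reason given for measuring depression is "as depression is a key confounder due to its correlation with fatigue".

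**The concern.** An effect modifier must be fixed before treatment starts. Randomisation then makes the arms comparable within each of its levels. The baseline half of the sentence meets this condition and the other half does not. A change in MDI, ESS or activity between Day 0 and Day 11 may be produced by the stimulation, and it may share causes with the change in FSMC. Active and sham patients who show the same change are then different kinds of patient, and their contrast is not a treatment effect in any identifiable group.

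The protocol itself allows for this. It treats ESS change and activity as outcomes that treatment may move, and it states that depression correlates with fatigue.

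At stake is the interpretation of a positive or negative trial. A real fatigue benefit could appear partly explained away by mood, sleep or activity. If stimulation improves mood but not fatigue, a difference against active treatment could appear.

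**Working it through.** **1. The protocol's own figure.** Sample size calculation uses a 10-point difference, SD 12.5, 80% power and two-sided 0.05. The normal approximation gives n = 2 × (1.960 + 0.842)² × 12.5² / 10² = 24.5, so 25 per arm, as stated. The SD and the effect are carried forward.

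**2. Arm effect conditional on the change.** Let M be the change in the putative modifier, scaled to a within-arm SD of 1. Let a be the shift in M caused by active stimulation, in SD units (negative = improvement), and ρ the within-arm correlation of M with FSMC change. With true effect τ, the arm coefficient once M is held fixed is

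τ − ρ × 12.5 × a.

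The protocol gives neither ρ nor a, so both are assumptions and a range is shown.

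| True effect τ | ρ | a | Conditional arm effect |
|---|---|---|---|
| -10 | 0.3 | -0.2 | -10 + 0.75 = -9.25 |
| -10 | 0.3 | -0.5 | -10 + 1.875 = -8.1 |
| -10 | 0.5 | -0.5 | -10 + 3.125 = -6.9 |
| -10 | 0.5 | -0.8 | -10 + 5.0 = -5.0 |
| 0 | 0.3 | -0.5 | +1.9 |
| 0 | 0.4 | -0.8 | +4.0 |

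**3. Simulation check (25 per arm, 4,000 trials per scenario).** The within-arm correlation is about 0.4. The SD of MDI change is √(0.4² × 8² + 4²) = 5.1. FSMC change is regressed on arm, MDI change and their product.

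- *Every patient gains 10 points, and MDI falls by 4 on average.* The within-arm slope is 0.976, so the expected arm effect at zero MDI change is -10 + 0.976 × 4 = -6.1. The simulation gives -6.1, significant in about 35% of trials. The interaction is significant in 4.5%.
- *Mean gain of 10 points, with individual effects varying (SD 10) and no baseline modifier.* The arm effect at zero MDI change is about -3.8. The interaction is significant in about 14%.
- *No fatigue effect, but MDI lowered by 4 points.* The arm effect is +3.9, significant in 17%. The interaction is significant in 4.9%.

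**4. The interaction test (29 per arm, 2,000 runs).** If treatment shifts only the mean of M, the interaction rejects in 4.8% to 6.4% of runs, even at a = -1.0. If treatment also multiplies the SD of M by k with ρ held fixed, the slope in the active arm becomes ρ × 12.5 / k. At ρ = 0.5 and k = 1.5 the interaction is then 6.25 × (1/1.5 − 1) = -2.1, which the simulation reproduces. Rejection is 7% to 29% at k = 1.5 and 10% to 61% at k = 2.0, for ρ from 0.3 to 0.7. A median split on M stayed near 5% in these scenarios.

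**5. Baseline modifiers only.** Randomisation makes a = 0 and the spread equal. The simulated arm effect is -9.98 to -10.10 and the interaction rejects in 4.8% to 5.0% of runs.

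**The case against.** The strongest reply is that the protocol asks whether effects differ by these factors. That is the arm-by-factor interaction, whereas most of the bias figures are for the arm coefficient at zero change, from a model the article does not specify. This stands: under a mean shift alone the interaction test keeps close to its nominal level. In the 14% scenario, individual effects really do vary, so the test picks up true variation through a downstream marker. The label of modifier is still wrong there, because no baseline trait modifies the effect.

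The reply also holds that the analyses are exploratory, corrected for multiplicity and kept out of the primary model, and that a mediation framework could sit in a statistical analysis plan not shown. The containment is real and keeps the point minor. However, multiplicity correction does not remove bias, and naming changes as modifiers is a choice this text makes, not a detail left open.

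Three stronger readings are tempting and not supported:

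- **That the effect would be halved or reversed.** Halving the 10-point effect needs, for example, ρ = 0.5 with a shift of 0.8 SD. Reversing it needs ρ × |a| above 10 / 12.5 = 0.8, for example 0.6 × 1.5 SD, which is implausibly strong. For a true effect of -5 the threshold falls to 0.4, but that is not the design effect. Excluding MDI of 26 or more at entry also limits room for a large fall.
- **That calling depression a confounder is an error.** Baseline depression does not systematically confound a randomised arm contrast. It can confound the planned correlation between metabolite shift and fatigue reduction, so the word is not simply wrong.
- **That "There are no plans for predetermined subgroup analyses" contradicts the modifier analyses.** Interactions with continuous baseline scores define no subgroups; this is at most a tension in wording.

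**Conclusion.** Wrong as written, of minor severity, and confined to exploratory analyses. The baseline half of the modifier sentence is sound. The half on changes compares arms within levels of variables measured after allocation, and the result cannot be read as a treatment effect.

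The direction of the bias follows if stimulation improves these variables and they move with fatigue: the conditional benefit shrinks, or a null effect turns unfavourable. The figures of -9.3 to -5 for a true -10, and +2 to +4 for a true zero, rest on assumed correlations of 0.3 to 0.5 and shifts of 0.2 to 0.8 SD. They show what could happen and are not predictions for this trial. Inflation of the interaction test is conditional too: it needs treatment to change the spread of the factor's change or its association with fatigue change. The primary analysis and the sample size of 58 are untouched.

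**What to change.** 1. Delete the words *or changes* from the modifier sentence in Statistical methods and analysis. Restrict the analysis to arm-by-baseline interactions: baseline MDI, baseline ESS, and accelerometer activity from D0 to before Day 1.
2. Compare Day 11 MDI between arms as an outcome, as is already planned for ESS change and activity.
3. If the link between these changes and fatigue change is wanted, report it separately as an associational or mediation analysis. State its assumptions, in particular no unmeasured common causes of the mediator and FSMC change, and include baseline FSMC and the baseline value of the mediator.

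The cost is wording only. All the baseline measures are already collected, and nothing changes in recruitment, visits or the primary analysis. What is lost is a modifier analysis whose result could not be interpreted as a treatment effect.

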#### Simulated E-fields

In addition to being an integral part of the intervention targeting algorithm, SimNIBS 4.5 allows for post-hoc simulation of the induced e-field for a given stimulation site. This allows important quality control for the *de facto* administered dose. The actual delivered electric field will be used in exploratory analyses of predictors of treatment effect.

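### Changes in depression, sleep and activity are listed as effect modifiers, but they arise after randomisation and cannot show effect modification (minor, exploratory only)

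*Protocol article*

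**What the plan says.** In Statistical methods and analysis, the protocol article keeps these factors out of the main model: "The primary analysis model will not adjust for depression, sleep, or physical activity measures". It then gives them another role: "These variables will be examined in exploratory analyses as potential modifiers of treatment response", with the aim "to assess whether treatment effects differ according to baseline levels or changes in these factors". The same section says that no subgroup analyses are predetermined and that exploratory analyses will be corrected for multiple comparisons.

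The timing of the measurements is given elsewhere:

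- **Allocation.** Under Allocation concealment and implementation, baseline behavioural and MRI assessments are finished before assignment, and envelopes are opened on the first intervention day.
- **Depression.** The Major Depression Inventory (MDI) is taken at baseline and at Day 11, the visit that also gives the primary FSMC score. The stated reason for measuring depression is "depression is a key confounder due to its correlation with fatigue".
- **Sleep.** The Epworth Sleepiness Scale (ESS) is taken at baseline and Days 6, 11 and 33. For ESS and MSIS-29 the plan is: "Both scales will be analyzed as change-from baseline comparison between groups at the main clinical follow-up". Diary sleep ratings are handled in the same way as diary fatigue, that is, as between-group differences in change.
- **Activity.** The accelerometer is worn from baseline to follow-up, through the intervention week, and between-group differences are to be assessed.

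**The concern.** An effect modifier must be something that treatment cannot move. Participants can be classified by baseline depression before allocation, and within each class the two arms remain comparable. Classifying them by how much their depression changed is different. If rTMS improves mood, active participants whose mood stayed the same are not the counterparts of sham participants whose mood stayed the same. Comparing FSMC between them mixes the treatment effect with that selection.

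At stake is how the exploratory results are read. A difference in effect between participants with more and less change in mood, sleep or activity could be reported as showing who responds to rTMS when it shows no such thing. The Discussion says that the findings are meant to inform later trials and the development of interventions, so such a reading would carry forward.

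**Working it through.** The plan gives no figure on this point. The check has two parts: whether the document supports each link needed for bias, and what follows under assumed values.

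**Links in the document**

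1. *The change comes after randomisation.* Baseline assessments precede assignment, and every second measurement follows it (Allocation concealment and implementation; Depression, quality of life, and sleep; Accelerometer-based outcomes).
2. *Treatment may move the factor.* Participant timeline refers to reported after-effects of neuromodulation in depression as well as in MS fatigue. The protocol also compares changes in ESS, diary sleep and activity between arms, so it allows that treatment may affect them.
3. *The factor is related to the outcome.* Depression is said to correlate with fatigue, and the accelerometer section says that higher activity goes with lower fatigue.
4. *No method is stated that would make conditioning on a change valid.* The article names no mediation or other causal framework for it.

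**Illustration**

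Inputs from the document (Sample size calculation): effect 10 FSMC points, SD 12.5. Assumptions not in the document: treatment improves the factor by δ = 0.5 SD; the within-arm correlation between change in the factor and change in FSMC is ρ = 0.3 or 0.5, through a shared cause.

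Let A be arm (1 = active), M the change in the factor (SD 1, lower is better, shifted by −δ in the active arm) and Y the change in FSMC (SD 12.5, lower is better, shifted by −τ in the active arm). Every participant has the same effect −τ, so there is no true modification. Then

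E[Y | A, M] = 12.5ρM + (12.5ρδ − τ)A.

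The effect of arm at a fixed value of M is 12.5ρδ − τ, not −τ.

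| | ρ = 0.3 | ρ = 0.5 |
|---|---|---|
| Offset 12.5 × ρ × 0.5 | 1.9 | 3.1 |
| True effect 0 appears as | +1.9 | +3.1 |
| True effect −10 appears as | −8.1 | −6.9 |
| Offset if δ = 0 | 0 | 0 |

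Splitting at the median of M instead, a simulation of the same model with 2 million participants gives offsets of about 1.2 (ρ = 0.3) and 2.0 (ρ = 0.5) points in each half.

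In this model the arm-by-change interaction is zero: the bias is the same at every level of M. A false interaction needs a further assumption, for example that treatment also makes M more variable. If the part of M not shared with Y is 1.5 times as large in the active arm, the slope of Y on M is 12.5ρ in sham and 12.5ρ / (ρ + 2.25(1 − ρ)) in active:

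- ρ = 0.3: 3.75 in sham; 3.75 / 1.875 = 2.00 in active; difference −1.75 points per unit of M.
- ρ = 0.5: 6.25 in sham; 6.25 / 1.625 = 3.85 in active; difference −2.40.

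Modification would then be reported although the FSMC effect is the same in everyone.

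**The case against.** The strongest reply is that little depends on this. The analysis is labelled exploratory, lies outside the primary model and is to be corrected for multiplicity. The bias disappears if treatment does not affect the factor. A false interaction, as distinct from a shifted effect at each level, needs still more assumptions. The detailed modelling of changes may also sit in an analysis plan that is not shown, and between-arm comparisons of ESS, diary sleep and activity are already planned.

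Most of that stands, and it limits the severity. It does not rescue the wording. Multiplicity correction controls chance findings and does nothing about a comparison that is no longer randomised. The article does not leave the role of the changes open either: it states that they will be used to see whether the treatment effect differs.

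A reader might go further and infer that the trial will report a depression-adjusted effect, because depression is called a key confounder. The text does not support this. That remark explains why depression is measured, and the primary model expressly leaves it out. For the same reason, a figure for how far adjustment would shrink the 10-point effect would describe an analysis that is not planned, and would need a correlation that the documents do not give.

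**Conclusion.** The point holds as a minor one, confined to exploratory analyses. Effects conditional on changes in depression, sleep or activity are open to bias and do not estimate effect modification; modification by baseline levels is sound. The bias is possible, not certain, and its size cannot be derived from the documents. The offsets of 1.9 to 3.1 points rest on the assumed δ and ρ and show only that the problem need not be trivial beside a 10-point target. The primary estimate and the sample size are unaffected.

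Two further inferences are not supported. A reader might say that biased subgroup results are planned, but the article speaks of modifiers and states that no subgroup analyses are predetermined. A reader might also extend the criticism to the delivered electric field, since "The actual delivered electric field will be used in exploratory analyses of predictors of treatment effect". That is a dose quantity, and nothing in the document suggests that the fatigue response alters it. The sentence can be read as an exploratory dose-response analysis within the active arm, which limits interpretation but is not the same fault.

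**What to change.** In Statistical methods and analysis, delete the reference to changes and restrict modifier analyses to baseline values, each tested as an arm-by-baseline interaction. Baseline values exist for all three factors: MDI and ESS at the baseline visit, and diary sleep and accelerometer activity from the interval before the first intervention day.

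Analyse the changes as outcomes by arm. This is already planned for ESS, diary sleep and activity; add change in MDI from baseline to Day 11. If the question is whether improved mood, sleep or activity carries part of the effect on fatigue, call it a mediation analysis and state its assumptions, including no unmeasured common causes of the mediator and fatigue.

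The cost is a change of wording and one added between-arm comparison on data already collected. The downside is that change-based results can no longer be reported as effect modification.

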### Methods: monitoring

#### Data monitoring

Confidential documents will be stored in a locked file, while the electronic information that can be traced to an identifiable person will be stored on a password-protected computer behind a secure “firewall” in accordance with the Danish Privacy Act.

#### Adverse events monitoring and harms

Minor discomfort due to peripheral co-activation from the rTMS treatment, e.g., scalp sensations; discomfort from peripheral electrical stimulation. Minor discomfort will be assessed with the TMS-Sens-Questionnaire (105), as described elsewhere in this protocol. Additionally, slight discomfort related to 7T MRI (see safety section) is expected.

All serious adverse events, or unexpected side effects will be reported to relevant authorities including the sponsor and the Danish Medicines Agency (in Danish: Lægemiddelstyrelsen). All adverse events will be recorded in the electronic clinical report form.

##### Safety

The utilization of non-invasive brain stimulation, in the form of TMS and rTMS, as well as 7T MRI, lead to specific safety concerns that require proper screening. TMS and rTMS are generally considered safe, according to latest guidelines (42), meta-analysis (117), and have also been shown safe in MS (45). Additionally, we will screen for adverse sensations using the TMSens questionnaire (105). 7T MRI is generally considered safe with proper precautions (56, 118), with few and not clinically relevant physiological side effects (119–121), no cognitive side effects (122), and is generally tolerated (122–124), including at our facility, in MS participants (112, 125).

##### Post-trial or ancillary care, in case of harm

All participants are covered by the general national insurance of the healthcare sector of Denmark (in Danish: Patientforsikringen).

#### Plans for auditing

The study is monitored within the department by members outside of the research project team. The medical ethics board may audit study documents at any time.

### Ethics and dissemination

#### Research ethics approval

This study has been approved by the national Medical Research Ethics Committee (in Danish: *Videnskabsetisk Medicinsk Komité*) under the Danish Health Authority (in Danish: *Sundhedsstyrelsen*) in September 2023 (ID 2309733), according to the Declaration of Helsinki. Ethics approval was amended in May 2024 and June 2025. Approval has also been granted by the Danish Data Protection Agency (ID: p-2023-14641). The study is pre-registered at ClinicalTrials.gov (ClinicalTrials.gov, ID: NCT06569550).

